## Abstract

**Background:**

Medication management in residential aged care facilities is an ongoing concern. Numerous studies have reported high rates of inappropriate prescribing and medication use in aged care facilities, which contribute to residents’ adverse health outcomes. There is a need for new models of care that enhance inter-disciplinary collaboration between residential aged care facility staff and healthcare professionals, to improve medication management. Pilot research has demonstrated the feasibility and benefits of integrating a pharmacist into the aged care facility team to improve the quality use of medicines. This protocol describes the design and methods for a cluster randomised controlled trial to evaluate the outcomes and conduct economic evaluation of a service model where on-site pharmacists are integrated into residential aged care facility healthcare teams to improve medication management.

**Methods:**

Intervention aged care facilities will employ on-site pharmacists to work as part of their healthcare teams 2 to 2.5 days per week for 12 months. On-site pharmacists, in collaboration with facility nurses, prescribers, community pharmacists, residents and families will conduct medication management activities to improve the quality use of medicines. Aged care facilities in the control group will continue usual care. The target sample size is 1188 residents from a minimum of 13 aged care facilities. The primary outcome is the appropriateness of prescribing, measured by the proportion of residents who are prescribed at least one potentially inappropriate medicine according to the 2019 Beers Criteria. Secondary outcomes include hospital and emergency department presentations, fall rates, prevalence and dose of antipsychotics and benzodiazepines, Anticholinergic Cognitive Burden Score, staff influenza vaccination rate, time spent on medication rounds, appropriateness of dose form modification and completeness of resident’s allergy and adverse drug reaction documentation. A cost-consequence and cost-effectiveness analysis will be embedded in the trial.

**Discussion:**

The results of this study will provide information on clinical and economic outcomes of a model that integrates on-site pharmacists into Australian residential aged care facilities. The results will provide policymakers with recommendations relevant to further implementation of this model.

**Trial registration:**

ACTRN12620000430932. Registered on 1 April 2020 with ANZCTR

## Background

Older adults residing in residential aged care facilities (RACFs) generally have complex co-morbidities and are prescribed a large number of different medications [1]. Studies have reported that, on average, RACF residents take between 9 and 11 regular medications [2–4]. Polypharmacy increases the risk of medication-related problems and adverse drug events, including hospitalisations, placing a significant burden on residents and economic cost on the health care system [5–7]. Australian studies have shown that almost all RACF residents have at least one medication-related problem [4, 8–11] and between 30% and 73% of residents are prescribed at least one potentially inappropriate medication (PIM) [4, 12–18]. According to a recent meta-analysis of 33 international studies, the use of PIM is significantly associated with an increased risk of hospitalisation in the older population, and the risk was higher in those who took more than one PIM [19]. Additionally, PIMs are associated with other potential adverse outcomes in older indivisuals, including fall, fracture, cognitive decline, delirium, stroke and cardiovascular events [20, 21].

Among PIMs, sedatives, antipsychotics and drugs with anticholinergic properties are particularly associated with greater risk of harm. A large Australian cohort study among 11,368 residents found that 61% were taking psychotropic medications, with the majority of these agents having sedative properties that can contribute to falls or confusion [22]. The over-use of psychotropic medications has been recently highlighted in the interim report of the Australian Royal Commission into Aged Care Quality and Safety [23]. Australian studies have reported that over 20% of RACF residents were taking antipsychotics regularly [22, 24], and the duration of antipsychotic use was longer than recommended [25–27]. Prolonged use of antipsychotics in older people is linked with increased risk of hospitalisation, hip fracture, peneumonia, stroke and death [28, 29]. Another large Australian study [30] of 17,000 RACF residents reported that 46% were taking drugs with moderate to strong anticholinergic effects; these drugs can contribute to cognitive and functional decline, delirium, worsening dementia, and increased mortality in older people [31].

Additionally, over-prescribing, using medicines longer than recommended, and drug interactions affect medication safety in aged care residents. The Australian 2018 Aged Care National Antimicrobial Prescribing Survey reported that 10% of residents were taking an antibiotic on the day of the survey, and about two thirds of these prescriptions were lacking relevant documentation of sign and symptoms to justify the need for antibiotic use [32]. Another large Australian study reported that more than 50% of residents were prescribed proton pump inhibitors with a median duration of use of 360 days in the year, while the recommended duration of use is 8 weeks [27]. Over-prescribing can also lead to unwanted drug interactions; a retrospective study of aged care resident’s medication records showed that 16% of residents were at high risk of drug-induced QT prolongation and potential arrhythmia due to polypharmacy [33]. Overall, many published studies highlight the need to improve medication management in RACFs. It is an area where pharmacists, doctors and nurses can work together, ensuring improved medication safety and quality use of medicines for residents [34].

Amongst the factors affecting medication safety and quality use of medicines in RACFs, lack of accessibility to pharmacists and doctors, and poor interdisciplinary collaboration were highlighted in a recent systematic review of international studies [35]. Consistent with these findings, the Australian Medical Association highlighted the “extremely urgent” need to increase the number of health care professionals in RACFs [36]. General practitioners (GPs), nurses and pharmacists are the key health professionals involved in the prescribing, administration and supply of medicines. Since these health professionals are generally not co-located, there are significant limitations in access, communication [37] and coordination of medication management processes [1] for aged care residents.

In Australia, there are two government-funded pharmacist-led services in place that aim to improve medication management in RACFs: (i) residential medication management review (RMMR) program [38] and (ii) quality use of medicine (QUM) service [39]. The RMMR for RACF residents has been in place since 1997 [37] and is similar to “clinical medication reviews” in the UK, “comprehensive medication reviews” in the USA and “MedsCheck LTC” in Canada [40–42]. The RMMR program enables GPs to refer RACF residents to accredited pharmacists to receive a medication review every 24 months or when there is a clinical need [43]. Although the RMMR service has been shown to be an effective strategy to identify and resolve medication-related problems and improve quality use of medicines for RACF residents [2], the service has logistical limitations. These include physical separation of community pharmacies, RMMR pharmacists and RACFs which leads to lack of timely access to pharmacist services when residents need them most [37]. Additionally, access to clinical pharmacists to conduct RMMRs for RACF residents is limited to periodic visits to the facility. Consequently, pharmacists performing RMMRs may not have a thorough understanding of the resident and may not be familiar with the facility staff and organisational structure, resulting in limited effectiveness of their activities within RACFs [44]. Other limitations of RMMR include limited involvement of pharmacists in the implementation and follow-up of recommendations and inconsistency in the level of collaboration between the health professionals in the RMMR processes [45]. QUM services are funded by the Commonwealth Department of Health for pharmacists to visit RACFS and conduct education to improve practices and procedures related to medication use. QUM services are intended to improve the medication management at the RACF level (e.g. through audits and staff education) [39, 46]; however, there has been little research to explore the effectiveness of this service [37].

Integrating an on-site pharmacist as part of the RACF health care team may address the gap in provision of medication management practices, policies and processes. On-site pharmacists, in collaboration with nurses, GPs, specialists, community pharmacists, residents and families will conduct medication management activities to improve the quality use of medicines at the facility [47–50]. This new model can improve communication among the healthcare team and enhance resident and family’s involvement in medication management decisions for individuals [48], leading to improved person-centred care. At the facility level, the on-site pharmacist can develop and enhance RACF policies and procedures for overall medication management [44]. These system improvement activities include reviewing and enhancing medication ordering, storage and administration processes, as well as conducting staff education, providing medication information, responding to medication utilisation reports, developing clinical referral pathways and contributing to staff and resident influenza vaccination.

A proposed model of integrated on-site pharmacist services into the RACF health care team was examined in a pilot study which was conducted by the lead author [47–51]. The conceptual foundation of the new model was to improve multi-disciplinary care, communication and collaboration in RACF’s healthcare team to enhance medication management [47, 48]. The findings of the pilot study indicated that the integration of a pharmacist into a RACF was feasible and acceptable to RACF staff, residents and GPs and resulted in improved medication administration and clinical documentation [47], increased provision of education for nursing and carer staff to promote the quality use of medicines and prevent medication administration errors [48], and enhanced staff influenza vaccination rates [49]. The positive findings of the pilot study informed the allocation of program funds from the Australian Department of Health to implement and evaluate this model in RACFs in the Australian Capital Territory (ACT).

The aim of this larger study is therefore to conduct a cluster randomised controlled trial (RCT) to evaluate if integrating pharmacists into RACFs, improves medication management in RACFs in the ACT, Australia. Objectives of the study include determining if this new integrated model (i) improves appropriateness of prescribing for RACF residents, as determined by the use of PIMs according to 2019 Beers Criteria [52], (ii) reduces RACF residents’ Emergency Department (ED) presentations and hospital admissions, (iii) improves other quality use of medicine indicators at the resident and facility levels, and (iv) is cost-effective.

## Methods

### Study design

This is a cluster RCT in RACFs in the ACT, Australia, with RACFs as the unit of randomisation. Participating RACFs will be randomised into either an intervention or control group. RACFs in the intervention group, in addition to ‘usual care’, will each employ an on-site pharmacist as member of the healthcare team. RACFs in the control group will continue ‘usual care’ that includes receiving government funded RMMR and QUM services from visiting pharmacists. Intervention and control groups will be recruited and randomised in staggered groups which will run in parallel.

### Participants

#### RACFs

All RACFs in the ACT that are nationally accredited facilities will be invited to participate in the trial. RACFs that have less than 20 beds will be excluded. There are a total number of 1978 RACF beds in facilities in the ACT, and the ACT had a population of 431,000 in 2020 [53].

#### Residents

Permanent residents of included RACFs will be included in the study unless they specifically request their data not to be included in the trial. Respite (non-permanent) residents will be excluded.

#### Pharmacists

Qualified pharmacists will be recruited through open expressions of interest sent to pharmacy professional groups and associations. The selection criteria for pharmacists include having registration with the Australian Health Practitioner Regulation Agency, accreditation to conduct medication reviews by the Australian Association of Consultant Pharmacy or equivalent hospital or geriatric clinical pharmacy experience, and accreditation to conduct vaccination. A list of eligible pharmacists will be provided to the intervention RACFs, who will employ pharmacists as per their organisational policy. Salaries for pharmacists will be funded by the research grant; however, they will be directly employed by RACFs as RACF staff members.

### Recruitment process

All RACFs in the ACT, Australia, that meet the inclusion criteria will be invited to participate in this study. After being provided information on the nature of the study and data required, each RACF will agree to participate through a signed contract. Recruitment will be staggered over a period of 6 months or until the sample size achieved. The recruitment and study timelines are shown in Fig. 1.

**Fig. 1 Fig1:**
[figure not shown]
Study timeline

### Randomisation and blinding

Randomisation will be at the facility level. RACFs will be randomised into either intervention or control group through computer-generated allocation by an independent researcher external to the research team. Randomisation will be stratified by size of facility. Due to the nature of the intervention, the trial participants will not be blinded.

### Intervention and model of care

RACFs in the intervention arm will have a pharmacist employed by their organisation as part of their health care team for 2 to 2.5 days a week for 12 months. Intervention pharmacists can work in up to 2 RACFs. Pharmacists will report to RACF managers. They will conduct resident and facility level activities that are within their current scope of practice as a health professional registered with Australian Health Professional Registered Agency.

The intervention (model of care) was informed by the findings from the pilot study [47–51] and discussion with RACF managers, GPs, pharmacists and a consumer representative who participated in the pilot. Components of this model of care are informed by integration of pharmacists into non-dispensing primacy care roles [37, 54]. Components and how they differ from usual care are presented in Table 1.

**Table 1 Tab1:** Key components and comparison between existing and proposed model

Key component	Existing model	Proposed model
Governance and service structure	RMMR & QUM activities are conducted by independent pharmacist (who are contractors) on visitational basis.	Pharmacist is employed by the RACF and is incorporated into RACFs care team. Pharmacist works within RACFs clinical governance structures.
Multi-disciplinary care (including resident and family)	Pharmacist is not incorporated into the RACF care team. They visit RACF at semi-regular intervals, provide medication advice to GPs through RMMRs and provide quality improvement projects.	Pharmacist is incorporated into the RACF care team and has contact with residents, families, GPs and prescribers, nurses and care staff. The pharmacist is available on-site at RACFs and involves residents and families into decision-making processes to improve medication management.
Reciprocal interdependence	Pharmacist provides medication review as an add-on service to assist GPs with quality of prescribing. However, they are not incorporated into the RACF care teams.	Multi-disciplinary team members, including pharmacists, nurses, carers, GPs and prescribers, community pharmacists, residents and families engage in shared decision making and work together to achieve goals.
Communication	Pharmacist communicates medication-related issues about individual residents to the GPs, usually through RMMR. GPs communicate medication changes to RACF nurses.	Pharmacist communicates and coordinates medication-related issues directly with GPs, nurses, carers, residents, community pharmacy and hospital.
Collaboration	Pharmacist usually collaborates with GPs to conduct RMMR.	Pharmacist closely collaborates on a regular basis with nurses, aged care staff and management, GPs and other prescribers, visiting pharmacists, community pharmacy, residents, families and hospital.
Sharing and access to information	Pharmacist has limited access to residents’ clinical records, which may include laboratory reports, while GPs and nurses have full access to clinical records.	All team members, including the pharmacist, will have full access to residents’ records, current medication lists, information about allergies, lab results, notes, procedures, and hospital discharge summaries.
Coordinated care/outcomes	Pharmacist provides once-off advice and opinion to GPs in RMMRs (including 2 follow-ups) but are not involved in implementing medication management changes or ongoing monitoring.	Residents’ treatment goals and outcomes are coordinated within the team of nurses, carers, pharmacist, GPs and other service providers. Pharmacist is involved in providing advice to GPs, prescribers and the RACF care team, and in implementing residents care plans and goals of care. Pharmacist also contributes to improving RACF medication management policies and procedures.

Pharmacist activities in intervention RACFs include the following:
Performing medication reviews in collaboration with residents, families, prescribers and nursesIdentifying residents at high risk of medication-related harm and hospitalisation, and prioritising interventions to address themMedication reconciliation and review at transition of careParticipating in case conferences with GPs, palliative care team, families and residentsReviewing and optimising medication administration roundsUpdating and improving resident records including clinical and care informationAnswering medication-related queries from residents, families and staffConducting regular clinical audits to identify medication-related problemsEducating residents, families and RACF staff about medication-related issuesImproving the RACF’s medication management policies and proceduresParticipating in relevant RACF committees and meetings including Medication Advisory Committee, Quality and Safety meetings, Falls Review Committee, and Medication Incidents Review CommitteeImproving influenza vaccination rates of staff and residents

Pharmacists in intervention sites will not be permitted to conduct RMMR or QUM services. RACFs will receive these services from existing providers as a part of usual care.

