### Sample size

It was estimated that a conventional RCT with randomisation of individuals would be able to detect a reduction from 60 to 40% of residents having at least one PIM [14], with a minimum of 106 residents in each arm (total of 212 residents in both arms) with a significance level of 5%, a power of 80% on equal allocation and a response rate of 85%. By adjusting for the loss of power due to clustering, with an intra-cluster correlation coefficient of 0.05 and a cluster size of 93 residents per RACF, the estimated sample size is (1 + [(93–1) x 0.05] =5.6 x 106) or 594 residents in each arm (1188 in both arms), equating to a minimum of 13 sites. The sample size was calculated using G*Power 3.1.9.4 [57].

The estimated prevalence of PIM in RACFs at baseline (60%) was based on previous studies in which the prevalence of PIM in Australian RACF residents were reported as 73% in 2018 [16], 49% in 2014 [14] and 56% in 2012 [58].

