### Statistical analysis

Descriptive statistics will be used to summarise and compare the data at the RACF level in each group at baseline and at the end of the trial, including primary and secondary outcomes as well as additional potential confounder variables (such as demographic profile, duration of residency, presence of dementia, Charlson comorbidity index [59] and number of medical conditions).

Bivariate analyses for group comparisons will use either t tests or ANOVA for data that are normally distributed, Mann-Whitney U and Kruskall-Wallis tests for data that are not normally distributed, or chi-square-based analysis for categorical outcome data. For within group comparisons, paired t tests and repeated measures ANOVAs will be used; if variables are not normally distributed, the Wilcoxon signed-ranks and Freedman tests will be used, while the McNemar test will be used for changes in proportions.

To determine the effect of the intervention on the outcome measures and the changes over time (between-within group effects), multilevel modelling methods, which take into consideration the hierarchical structure of the data (including clustering within RACF and repeated measurement occasions) will be applied. These modelling methods will include mixed-effects generalised linear models (Logistic and Poisson regression models) for binary and count outcomes as well as mixed-effects linear models for continuous outcomes assumed to have a normal distribution, or otherwise transformed to meet the assumption.

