The study is using a staggered approach to the recruitment and intervention. Due to the impact of the recent COVID-19 pandemic on RACF’s workforce and operations, this staggering will provide the facilities with time to prepare and adapt to recent policy and procedural changes. These changes may impact on the study outcomes; for example, there may be changes in the number of regular healthcare staff in RACFs or residents may receive fewer GP and other visiting healthcare professional visits and this may impact the level of collaboration with pharmacists. Potential restrictions in visiting RACFs due to COVID-19 pandemic may affect the data collection processes. On-site pharmacists participating in this study will have accreditation to conduct medication review; however, they may be at different level of experience and skills, which may impact the quality of pharmacist activities in some RACFs. This will be further explored by assessing the fidelity of interventions that determines whether the intervention was conducted as planned across the intervention RACFs and includes an audit on the appropriateness of pharmacists’ medication reviews. Participating RACFs will be all within ACT which is a metropolitan area in Australia; thus, the findings may not be generalisable to RACFs located in rural and remote areas.

A number of limitations should be noted. PIMs are a proxy measure for appropriateness of prescribing, which represents an ideal level of care and is reliable in predicting adverse events [62]. The study does not include measurements of resident focused indicators such as Quality of Life, noting the difficulties in seeing changes in elderly frail population. The reporting of secondary outcomes is based on facility records, which may be under reported.

The study provides important information on clinical and economical outcomes of the model where on-site pharmacists are integrated into RACFs’ health care team to improve medication management. The results will provide policymakers with recommendations relevant to the potential further implementation of this model.

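### If intervention pharmacists are shared between two facilities and differ in effect, treating the facility as the highest independent unit understates the standard error

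*Protocol article*

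**What the plan says.** All of this is in the protocol article.

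- **Intervention and model of care.** Each intervention facility has a pharmacist "for 2 to 2.5 days a week for 12 months", and "Intervention pharmacists can work in up to 2 RACFs". Two facilities would make 4 to 5 days, close to a full-time post. Sharing is permitted, not required, and its expected extent is not given.
- **Randomisation and blinding.** "Randomisation will be at the facility level".
- **Sample size.** There is one level of clustering, the facility, with an intra-cluster correlation of 0.05 and 93 residents per facility. The result is 594 residents per arm and at least 13 sites.
- **Statistical analysis.** The multilevel models reflect the hierarchy of the data, "including clustering within RACF and repeated measurement occasions". No pharmacist level is named.
- **Discussion.** Of the pharmacists, the authors write that "they may be at different level of experience and skills, which may impact the quality of pharmacist activities in some RACFs". The stated response is the fidelity assessment.

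**The concern.** The intervention is one person's work: medication reviews, audits, education, policy. Two facilities with the same pharmacist share that person's skill, so their outcomes are correlated beyond what the facility level captures. The control arm has no counterpart.

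At the minimum of 13 sites, the intervention arm has about 6 or 7 facilities, which could be served by as few as 3 or 4 people. A model that stops at the facility counts an unusually good or poor pharmacist twice. The interval for the average effect of the model of care is then too narrow, and one person's skill can be read as an effect of the model. The average effect is what the article promises policymakers.

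**Working it through.** **1. The plan's own figure.** Design effect 1 + (93 - 1) × 0.05 = 5.6. Then 5.6 × 106 = 593.6, rounded to 594 per arm and 1188 in total. 1188/93 = 12.8, so 13 sites. The figure reproduces, and the facility is the only cluster level in it.

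**2. Layouts (assumed).** The split of 13 sites by arm is not stated, so I take 7 intervention and 6 control, or 6 and 7. Maximum sharing is then 2+2+2+1 (4 pharmacists) or 2+2+2 (3 pharmacists).

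**3. Effect on the pharmacist component.** If pharmacist k serves s_k of n facilities, that component of the arm-mean variance is multiplied by Σs_k²/n.
- 2+2+2+1: (4+4+4+1)/7 = 13/7 = 1.86
- 2+2+2: 12/6 = 2.0

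These factors apply to the pharmacist component only, not to the whole variance.

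**4. Effect on the standard error of the arm difference.** Hold the total correlation at 0.05 and let f be the share of intervention-arm between-facility variance due to the pharmacist. The documents give no value for f. With p(1-p) = 0.24 at both 60% and 40%:

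Var(intervention mean) = 0.24 × [0.95/(93n) + 0.05(1-f)/n + 0.05f × Σs_k²/n²]

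For 7 facilities, 4 pharmacists, f = 0.5:
- Facility-only intervention variance: 0.24 × (0.95/651 + 0.05/7) = 0.002065
- Control variance, 6 facilities: 0.24 × (0.95/558 + 0.05/6) = 0.002409
- Facility-only SE: √0.004473 = 0.0669
- True intervention variance: 0.24 × (0.001459 + 0.003571 + 0.025 × 13/49) = 0.002799
- True SE: √(0.002799 + 0.002409) = 0.0722, a ratio of 1.08

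| Layout | f | True SE / facility-only SE | Power (normal approximation) |
|---|---|---|---|
| No sharing, or f = 0 | any / 0 | 1.00 | 85% |
| 7 facilities, 4 pharmacists | 0.1 | 1.02 | 84% |
| 7 facilities, 4 pharmacists | 0.5 | 1.08 | 79% |
| 6 facilities, 3 pharmacists | 0.1 | 1.02 | 83% |
| 6 facilities, 3 pharmacists | 0.5 | 1.11 | 77% |

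**5. Error rate.** This comes from a simulated pooled t-test on facility values, testing no average effect at a nominal 5%. Control-facility variance is 1, and pharmacist variance ρ/(1-ρ) is added in the intervention arm. This differs from step 4: the intervention arm becomes more variable, and the variance is estimated from few facilities.

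| Layout | ρ = 0.1 | ρ = 0.3 | ρ = 0.5 |
|---|---|---|---|
| 2+2+2+1 v 6 controls | 5.4% | 6.5% | 8.1% |
| 2+2+2 v 7 controls | 5.7% | 7.7% | 10.8% |

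- Without sharing, 7 v 6 stays at about 5% or slightly below. For 6 v 7 it is already 5.1-5.7%, because the smaller arm has the larger variance. That part of the 10.8% is not due to sharing.
- With one shared pair among seven, the rate is 5.1-5.6%. With one pair among six (v 7), rerunning the simulation gave 5.3-7.3%, on that higher baseline.

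**6. Does the remedy work?** Treating facilities with a common pharmacist as one unit, with unequal-variance degrees of freedom, brings the rate to about 4.4-6.0% at maximum sharing.

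**The case against.** **Sharing is allowed, not planned.** Each facility hires from a list under its own policy, and no number of shared posts is given. This stands. A reader might infer that the trial's error bars are too small as a matter of fact. The documents do not support that, because both the extent of sharing and the pharmacist's share of variance are unknown.

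**The null is a particular one.** If pharmacists have no effect at all, they cannot differ in effect and nothing is inflated. Randomisation by facility remains valid. This also stands: the problem concerns inference about the average effect and the interval width, not the validity of the allocation.

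**The analysis plan may settle it.** The wording on model levels is open-ended, and an unseen document may name another level. That is fair as far as it goes. But this article itself fixes the sharing rule, a sample size with one cluster level and the levels it names, and these do not fit together.

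**Pharmacist differences are already examined.** Daily diaries, facility fidelity ratings and an audit of medication reviews are planned. They describe delivery but do not correct a standard error. The diaries may let the pharmacist-facility link be recovered, but the data collection table does not list it.

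**A pharmacist random effect would be fragile.** This stands. In a simulation with three pairs, the pharmacist variance was estimated as zero or negative in 48%, 37% and 26% of runs at shares of 10%, 30% and 50%.

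**Conclusion.** The concern holds conditionally. The plan permits sharing, expects pharmacists to differ, and names no level above the facility. If sharing occurs and pharmacists differ in effect, the facility-only standard error is too small.

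At maximum sharing with 13 facilities and an assumed pharmacist share of 10-50%, the true standard error is about 2-11% larger. The true error rate is about 5.4-8% with 7 facilities and 4 pharmacists. It is about 5.7-11% with 6 facilities and 3 pharmacists, where unequal variances alone give 5.1-5.7%. One shared pair among seven facilities leaves it at or below about 5.6%. No sharing, or no pharmacist effect, leaves no understatement from this source.

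The arm split, the sharing pattern and the variance share are all assumptions. The factors 1.86 and 2.0 should not be read as inflation of the total variance.

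**What to change.** 1. Record which pharmacist serves each intervention facility, with dates if this changes.
2. Report the number of pharmacists alongside the number of facilities.
3. If any pharmacist is shared, add an analysis in which facilities with a common pharmacist form one cluster and each control facility is its own cluster. Base standard errors and small-sample degrees of freedom on those clusters, allowing unequal variance between arms.
4. Do not rely on a pharmacist random effect alone. With at most three pairs, its variance will often be estimated as zero, and the result would fall back to the facility-only one.

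The cost is one identifier and one further analysis. Intervals become somewhat wider. At maximum sharing the intervention arm contributes 4 units instead of 7 (3 within-arm degrees of freedom instead of 6), or 3 instead of 6 (2 instead of 5). The link is easiest to capture while the pharmacists are in post.
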